## Abstract

**Background:**

*De Qi* is a special sensational response upon acupuncture needling. According to traditional acupuncture theory, the treatment is “effective only after *Qi* arrival”; that is, *De Qi* is an important indicator of therapeutic efficacy and good prognosis. However, it is still disputable whether *De Qi* improves the efficacy of acupuncture therapy. This prospective, randomized controlled trial aims to explore the influence of *De Qi* induced by acupuncture on immediate and accumulated analgesic effects in patients with knee osteoarthritis (KOA).

**Methods/design:**

Eighty-eight patients with KOA will be recruited and randomly assigned to the *De Qi* group (enhanced stimulation to evoke *De Qi*) and the control group (weak stimulation to avoid *De Qi*) in the Department of Acupuncture and Physical Therapy, Beijing Luhe Hospital Affiliated to Capital Medical University. Each patient will receive three 30-minute sessions per week for 4 consecutive weeks and undergo a 1 month follow-up. The severity of knee pain, as measured on a 100-mm visual analog scale (where 0 indicates no pain and 100 indicates intolerable pain) will be used as the primary outcome, and the Knee injury and Osteoarthritis Outcome Score will be used as the secondary outcome. Both indexes will be measured before and after the 1^st^ (for evaluating the immediate analgesic effects), 3^rd^, 6^th^, 9^th^, and 12^th^ (for evaluating the accumulated analgesic effects) treatments and at the end of the follow-up. The intensity of the *De Qi* sensation will be assessed by the Chinese-Modified Massachusetts General Hospital Acupuncture Sensation Scale at the end of each treatment. Side effects during the treatments will be recorded and analyzed as well. The comparisons between the *De Qi* group and the control group will be done by using both an intention-to-treat analysis and a per-protocol analysis.

**Discussion:**

This prospective randomized controlled study will be helpful in enhancing our understanding of the analgesic effect of *De Qi* on patients with KOA and may provide a clinical basis for further investigation of the relationship between *De Qi* and the therapeutic efficacy of acupuncture, thereby offering some evidence for the role of *De Qi* in an efficacious acupuncture therapy.

**Trial registration:**

Chinese Clinical Trial Registry, ChiCTR-IIR-16008972. Registered on 4 August 2016 Additional file 2.

**Electronic supplementary material:**

The online version of this article (doi:10.1186/s13063-017-1975-7) contains supplementary material, which is available to authorized users.

## Background

As one key component of traditional Chinese medicine, acupuncture has made indelible contributions to human health during the thousands of years’ development of medicine. *De Qi*, also called “*Qi* Arrival” in ancient literature and recently “acupuncture sensation,” refers to the reaction of meridian *Qi* at the needling site after the insertion of the needle to a certain depth with various manipulations by the acupuncturist, namely, lifting, thrusting, twisting, and rotating. At the same time, the patients often perceive soreness, numbness, fullness, and heaviness, while the acupuncturists often experience a sensation of heaviness, tightness, or stagnation at the hand [1].

Considered as an important indicator of therapeutic efficacy, *De Qi* has been emphasized by acupuncture practitioners over the ages. In the meanwhile, researchers have attempted to investigate the correlation between *De Qi* and the therapeutic efficacy of acupuncture. While many studies have suggested that *De Qi* helped improve the efficacy [2–4], some high-quality studies concluded otherwise [5–7]. As of today, it remains controversial whether or not *De Qi* contributes to the therapeutic effect of acupuncture [8–10]. In light of recent developments of evidence-based medical research and the related investigative techniques, this topic has become a focus of attention in the modern acupuncture field [11, 12].

Knee osteoarthritis (KOA), also called degenerative arthritis and osteoarthritis, is a chronic joint disorder caused by degenerative disease in the knee synovium. Characterized by degeneration of articular cartilage and osteosclerosis/hyperosteogeny [13], it is the most common chronic, progressive, and degenerative joint disease in the population aged 40 and older. The main clinical manifestations of KOA include aching, movement disorders, and joint deformation [14]. It has become a growing concern for public health in aging societies worldwide. According to an epidemiological study from Manchester University, UK, KOA is the 4^th^ and the 8^th^ cause of labor loss in males and females, respectively, in western countries. Epidemiological data from China showed that KOA occurred in 85% of people more than 65 years old [15]. So far there is no especially effective treatment for this disease. From the point of view of traditional Chinese medicine, KOA can be categorized as a bone impediment. According to multiple research studies, acupuncture has a good therapeutic efficacy on bone impediments, including KOA [16–18] Additional file 2.

In this research, we will use both strong stimulation to evoke *De Qi* and weak stimulation to avoid *De Qi* during the acupuncture treatment of KOA. We will compare the immediate and the accumulated analgesic effects between the two groups in order to explore the correlation between *De Qi* and the therapeutic efficacy of needling at certain acupoints, thereby providing a clinical basis for further mechanistic studies of *De Qi* Additional file 2.

## Methods/design

### Overview

This study is a prospective, randomized controlled trial that compares the therapeutic outcomes in the presence and absence of *De Qi*. The trial will be carried out at the Department of Acupuncture, Beijing Luhe Hospital Affiliated to Capital Medical University, Beijing, China Additional file 2. The procedure will last 14 weeks, which consists of a period of pre-randomization adaptation for 2 weeks, followed by a 4-week acupuncture therapy after the randomization, and finally a 1 month follow-up (Fig. 1) Additional file 2.

**Fig. 1 Fig1:**
[figure not shown]
Flow chart of the trial. *KOA* knee osteoarthritis, *VAS* visual analog scale, *KOOS* Knee injury and Osteoarthritis Outcome Score, *C-MMASS* Chinese-Modified Massachusetts General Hospital Acupuncture Sensation Scale

The trial follows strictly the guidelines of the Declaration of Helsinki (Version 2000) and has been approved by the Ethics Committee of Beijing Luhe Hospital Affiliated to Capital Medical University (Approval Number 2016-LH-WZ-002). Each patient will be informed both orally and in writing with complete details about the procedure, the possible risks, the voluntary nature of the participation, and the right to withdraw at any moment prior to enrollment Additional file 2. Informed consent will be required to be signed by each patient before his/her entry into the trial and will be kept in the research archives.

### Subjects

A total of 88 patients diagnosed with KOA will be included in the trial. The diagnostic criteria for KOA are as defined by the American College of Rheumatism [19]: (1) knee pain most of the time; (2) crepitus in motion; (3) less than 30 minutes of morning stiffness; (4) patient more than 38 years old; (5) bone enlargement. Patients who meet criteria (1)–(4) or (1) + (2) + (5) or (1) + (4) + (5) are diagnosed with KOA.

### Inclusion criteria

Patients to be recruited in this study should meet the diagnostic criteria, which include: diagnostic criteria of KOA; age 30–70 years; recurrent pain in unilateral or bilateral knee joint(s) for more than 1 month; average intensity of knee pain measured by a 0–100 mm visual analog scale (VAS ) equal to or greater than 30 mm in the last month before randomization; good health in general; not receiving medication or other treatments for at least 2 weeks prior to inclusion into the trial; written consent to participate in the trial Additional file 2.

### Exclusion criteria

Patients with any of the following conditions will be excluded: manifestation of joint space narrowing, chondral sclerosis and/or cystic degeneration, osteophyte formation at the edge of the joint; infectious, gouty, rheumatoid, or traumatic arthritis; known life-threatening diseases, mental illnesses, or neurological disorders such as Alzheimer’s disease and Parkinson’s disease; pregnancy or anticipation of pregnancy; concurrence of pain(s) on other site(s); inability to complete the treatment course or to be evaluated for therapeutic efficacy Additional file 2.

### Sample size

Patients with KOA will be randomized into two groups in a 1:1 ratio. The sample size for each group was calculated according to the following equation for a design with repeated measures [20] Additional file 2:$$ \mathrm{n}=\frac{2\kern0.5em *\kern0.5em {\upsigma}^2\kern0.5em {\left({\mathrm{u}}_{\alpha}\kern0.5em +\kern0.5em {\mathrm{u}}_{\upbeta}\right)}^2}{\updelta^2}\left\{\left[\frac{1}{\mathrm{r}}+\left(1-\frac{1}{\mathrm{r}}\right)\uprho \right]-\frac{\uprho^2}{1/ P+\left(1-1/ P\right)\rho}\right\} $$

where *P* stands for the number of observations prior to acupuncture (VAS score before the first intervention, one time point before treatment), and *r* is the observation number after acupuncture (VAS scores at the end of the 1^st^, 3^rd^, 6^th^, 9^th^, and 12^th^ treatments, a total of five time points after treatment). The values of ρ, α, μ_α_, and μ_β_ used here are as follows: ρ = 0.70 (usually between 0.50 and 0.75); α = 0.05 (bilateral); μ_α_ = 1.96; μ_β_ = 0.8417. As a result, an estimated sample size of 37 patients per group was obtained, assuming that a minimal difference of δ = 10 mm is considered as a clinically significant relief of chronic pain, as recommended by IMMPACT [21], and with a standard deviation (σ) of 29.5 mm of the VAS score for knee pain in all patients prior to treatment, according to the data from the clinical trial run by White et al. [22]. Considering a possible loss to follow-up of 20% Additional file 2, we planned to include total of 88 patients in our study.

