### Statistics

All data will be analyzed using SPSS for Windows 17.0 Software (SPSS Inc., Chicago, IL, USA). For the main analysis, we will perform both an intent-to-treat principle and a per-protocol analysis. Measurement data will be described with mean ± standard deviation ($$ \overline{x} $$ ± SD), and count data will be expressed with number of cases and percentages. All statistical analyses will use two-tailed tests, and the level of significance will be set at *p* < 0.05 Additional file 2. 

Demographic and baseline characteristics of study participants by randomization group will be analyzed by an independent sample *t* test, *t*' test, or nonparametric test. In the comparison between the *De Qi* and control groups, the primary outcome (VAS scores) and secondary outcome (KOOS, in the form of symptom scores) will adopt the method of within-subject 6 × 2 factorial repeated measures analysis of variance (ANOVA) to analyze the integral analgesic effect, where the factors are time (six levels: baseline, and at the end of the 1^st^, 3^rd^, 6^th^, 9^th^, and 12^th^ treatments) and group (two levels: *De Qi* group and the control group). The immediate analgesic effect will be evaluated by the VAS score after the first treatment; the accumulated analgesic effect will be rated by the VAS score after the last treatment. They will be analyzed by the independent sample *t* test and *t*' test or nonparametric test. In addition, the overall *De Qi* scores of each group, i.e., the sum of the scores of all sensations in each treatment, will be considered and analyzed with the primary outcome by a bivariate correlation test (described by *r* and *p*).

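### Optional gain in precision: the between-arm VAS comparisons adjust for no baseline value, although the pre-session-1 VAS and possibly the eligibility month-average VAS could serve as covariates

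*Protocol article*

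**What the plan says.** All references are to the protocol article.

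- **Sample size.** The repeated-measures formula has a term P for the number of readings before treatment. The article sets P = 1: "VAS score before the first intervention, one time point before treatment". It sets r = 5: "a total of five time points after treatment". One correlation, 0.70, serves for every pair of readings.
- **Inclusion criteria.** Average knee pain on a 0–100 mm VAS must be "equal to or greater than 30 mm in the last month before randomization". The same section requires at least 2 weeks free of treatment before inclusion.
- **Knee pain intensity.** The outcome VAS is the pain the patient has at the time of measurement.
- **Initial visit.** Age, sex, disease course and body mass index are named among the information collected. The month-average VAS is not named.
- **Statistics.** The repeated-measures ANOVA uses "time (six levels: baseline, and at the end of the" 1st, 3rd, 6th, 9th and 12th treatments, crossed with group. The immediate and accumulated effects are VAS scores after the first and last sessions, compared by t, t' or nonparametric tests. No covariate appears in any of these comparisons.

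**The concern.** Two VAS values exist, or should exist, for each patient before treatment: the reading just before session 1 and the month average that decides eligibility. Both are likely to predict later VAS scores. The first enters the ANOVA only as one of six time levels and does not enter the two single-time-point tests at all. The second is not used after screening.

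Precision matters here because recruitment of 88 is already complete, so the analysis is where it can still be improved. With the plan's own 20% loss, 88 × 0.8 ≈ 70 patients remain, about 35 per group. That is under the 37 the plan calculates, with power of about 78% by its own formula.

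**Working it through.** **Inputs from Sample size:** σ = 29.5 mm, δ = 10 mm, ρ = 0.70, P = 1, r = 5, quantiles 1.96 and 0.8417. Powers below use the normal approximation, with σ and δ taken to apply at each time point.

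**1. The plan's own figure.** n = K × F, where

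K = 2 × 29.5² × (1.96 + 0.8417)² / 10² = 136.6

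F = [1/r + (1 − 1/r)ρ] − ρ² / [1/P + (1 − 1/P)ρ]

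With P = 1, F = (0.20 + 0.80 × 0.70) − 0.49 = 0.27 and n = 136.6 × 0.27 = 36.9, so 37 per group. The stated figure is reproduced. The 0.49 subtracted is the credit for adjusting the post-treatment average for one baseline reading.

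**2. First covariate, single-time-point tests.** Without adjustment the variance factor is 1. With the pre-session-1 VAS as covariate it is 1 − 0.70² = 0.51. With two interchangeable baselines it is 1 − 0.49/0.85 = 0.4235.

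| Model | Factor | Power, 44 per group | Power, 37 per group |
|---|---|---|---|
| Unadjusted, as planned | 1 | 35.6% | 30.8% |
| Pre-session-1 VAS | 0.51 | 60.5% | 53.3% |
| Both readings, best case | 0.4235 | 68.6% | 61.0% |

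At 44 per group the first covariate adds about 25 points and the second at most about 8 more.

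**3. Second covariate, post-treatment average.** Let c be the correlation of the month-average VAS with the pre-session-1 VAS, and q its correlation with each post-treatment reading. Then

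F = 0.76 − (0.49 + q² − 2 × 0.70 × c × q) / (1 − c²)

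The documents give neither c nor q, so the values below are assumptions. The comparator is a model already adjusted for the pre-session-1 VAS (F = 0.27, power 80.1% at 37 per group).

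| c | q | F | Power, 37 per group | Gain, points |
|---|---|---|---|---|
| 0.7 | 0.7 (same as P = 2) | 0.1835 | 92.6% | 12.4 |
| 0.6 | 0.6 | 0.219 | 87.6% | 7.4 |
| 0.5 | 0.5 | 0.240 | 84.5% | 4.4 |
| 0.6 | 0.5 | 0.260 | 81.6% | 1.5 |
| 0.7 | 0.5 | 0.270 | 80.1% | 0.0 |

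On powers rounded to whole percentages, the four weaker cases run from 80% to 88%, a gain of 0 to 8 points. At c = 0.7 and q = 0.49 the gain is exactly zero, because the month average then says nothing about later pain beyond what the pre-session-1 reading says.

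**4. Cost.** Going from one covariate to two inflates the variance by about (N − 4)/(N − 5): 1.2% at N = 88 and 1.5% at N = 70.

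**The case against.** The strongest objection is that nothing here is wrong. Only one reading of the outcome VAS precedes treatment, so P = 1 is correct and 37 follows from it. Choice of covariates is also often left to an analysis plan, which is not shown. The first part stands in full. The second stands in part: the article does name its tests, and none of them carries a covariate.

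Three stronger readings are tempting, and the documents do not support them.

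- **That P should be 2, so 26 per group would do (136.6 × 0.1835 = 25.1).** This needs two readings of the same quantity with the same variance and one common correlation. The eligibility value is a one-month average, cut off at 30 mm, and may cover time before the treatment-free 2 weeks. It is not interchangeable with pain at the moment of measurement.
- **That power would rise from 80% to 93% over the plan.** Both figures assume adjustment for the pre-session-1 VAS, which the Statistics section does not plan. They measure a second covariate against a first that is not there.
- **That the month-average value is already in the data set.** The eligibility rule implies that someone obtained it. The article does not say how the average was formed, or whether the number was kept rather than the criterion ticked as met. With recruitment complete, a value not kept could no longer be collected prospectively.

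In fairness to the plan, the group-by-time term of the ANOVA does use the baseline reading. The corresponding contrast, post-treatment average minus baseline, has factor 0.76 + 1 − 1.40 = 0.36, against 0.27 with covariate adjustment. Baseline is therefore used there, though less efficiently. It is not used in the two single-time-point tests.

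**Conclusion.** This holds as an optional improvement. P = 1 is correct for the outcome VAS. The month-average VAS is required for eligibility and then has no role, and no between-arm VAS comparison adjusts for a baseline covariate.

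Most of the gain comes from the pre-session-1 VAS: about 36% to 61% power for a single-time-point test with 44 per group. This rests on the plan's σ, δ and ρ holding at that time point, and on no loss of patients. The month-average VAS may add anything from nothing to about 8 points at 37 per group under the assumed weaker correlations. Twelve points is a ceiling that needs interchangeable readings at 0.70. Both values precede randomization, so adjusting for them in pre-specified models does not bias the comparison.

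**What to change.** Before unblinding, and before any outcome is compared between the coded groups, specify covariate-adjusted between-arm models for three VAS outcomes: the post-treatment average, the score after session 1 and the score after session 12.

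1. Enter the pre-session-1 VAS as the first covariate in each model.
2. Confirm whether the numeric month-average VAS was kept for all patients. If so, enter it as the second covariate. If not, stop at the first.
3. Leave P = 1 and the calculation of 37 per group as they are, and claim no reduction in sample size from the second covariate.

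The cost is one degree of freedom per covariate per model and a short addition to the analysis text. No new data are needed for the first covariate. For the second, that depends on the check in step 2.

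### The stated 80% power for 10 mm covers only the baseline-adjusted mean of five readings; for 10 mm at session 1 or at session 12, the immediate and accumulated effects, power is about 53–61% with baseline adjustment and 31–36% with the planned t test.

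*Protocol article*

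**What the plan says.** The Sample size section of the protocol article uses a repeated-measures formula with P = 1 pre-treatment reading ("VAS score before the first intervention, one time point before treatment") and r = 5 post-treatment readings ("VAS scores at the end of the 1^st^, 3^rd^, 6^th^, 9^th^, and 12^th^ treatments, a total of five time points after treatment"). The effect size enters once, "assuming that a minimal difference of δ = 10 mm is considered as a clinically significant relief of chronic pain", and is tied to no session. The outcome is that "an estimated sample size of 37 patients per group was obtained". After an allowance for 20% loss, the total is 88, or 44 per group.

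The Statistics section names three effects on the VAS:

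- An integral effect, analysed by repeated-measures ANOVA over baseline and the same five post-treatment readings.
- An immediate effect, taken from the VAS score after the first treatment.
- An accumulated effect: "the accumulated analgesic effect will be rated by the VAS score after the last treatment".

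The last two are compared between groups by an independent-sample t test, a t' test or a nonparametric test. No baseline adjustment is mentioned. The Abstract and the Discussion both give the aim of the trial as the immediate and accumulated effects.

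**The concern.** The sample-size passage reads as 80% power to detect a clinically relevant 10 mm benefit. With r = 5, however, the δ in the formula is the group difference in the average of five readings, from just after session 1 to session 12. The text does not say this. The two effects that make up the trial's stated aim are single readings, which vary more than a five-reading mean, so the same 10 mm is harder to detect in them.

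The practical risk lies in interpretation. If the session-12 comparison is not significant, a reader of the protocol could take it as 80%-powered evidence against a 10 mm benefit of De Qi, on a question that the Background calls controversial.

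**Working it through.** **Inputs, all from the Sample size section.** Correlation, significance level and normal quantiles: "ρ = 0.70 (usually between 0.50 and 0.75); α = 0.05 (bilateral); μ_α_ = 1.96; μ_β_ = 0.8417". Standard deviation: "with a standard deviation (σ) of 29.5 mm of the VAS score for knee pain in all patients prior to treatment". Difference 10 mm, r = 5, P = 1, allocation 1:1. Group sizes used below: 37 (as calculated), 44 (88 / 2) and 35 (44 × 0.8 = 35.2, completers after the assumed 20% loss).

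**Step 1: the plan's own figure.** The bracket in the formula is [1/5 + (4/5)(0.70)] − 0.70² = 0.76 − 0.49 = 0.27. Then

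n = 2 × 29.5² × (1.96 + 0.8417)² / 10² × 0.27 = 136.62 × 0.27 = 36.9, which rounds up to 37.

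The stated 37 is reproduced. The factor 0.27 is the variance, relative to σ², of the mean of five readings adjusted for one baseline reading. The 10 mm is therefore a difference in that mean.

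**Step 2: power for 10 mm under different targets.** Power = Φ(10/SE − 1.96), with SE = 29.5 × √(2f/n). For one reading (r = 1) adjusted for baseline, the same formula gives f = 1 − 0.49 = 0.51. For one unadjusted reading, f = 1.

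| Target, difference 10 mm | f | 35 per group | 37 per group | 44 per group | n per group for 80% |
|---|---|---|---|---|---|
| Five-reading mean, baseline-adjusted | 0.27 | 77.9% | 80.1% | 86.4% | 37 |
| One reading, baseline-adjusted | 0.51 | 51.0% | 53.3% | 60.5% | 70 |
| One reading, unadjusted t test | 1 | 29.4% | 30.8% | 35.6% | 137 |

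Example for one adjusted reading at 44 per group: SE = 29.5 × √(1.02/44) = 4.49 mm; 10/4.49 − 1.96 = 0.27; Φ(0.27) ≈ 0.605. The last column is 136.62 × f, rounded up. The single-reading rows apply equally to session 1 and session 12, because the protocol gives one σ and one ρ for all readings.

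**Step 3: sensitivity to ρ.** The protocol's usual range for ρ is 0.50 to 0.75. For one adjusted reading, f = 1 − ρ² then runs from 0.75 to 0.4375. At 44 per group, SE runs from 5.45 to 4.16 mm and power from 45% to 67%. Even the most favourable end stays below 80%.

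**Step 4: the five-reading mean if the benefit builds up.** The documents give no time course, so these profiles are assumptions. Each reaches 10 mm at session 12 and not more. The mean is taken over sessions 1, 3, 6, 9 and 12, and power uses f = 0.27.

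| Assumed profile | Mean, mm | Power at 37 | Power at 44 |
|---|---|---|---|
| 0 at session 1, then linear to 10 | 4.73 | 26% | 30% |
| Proportional to session number | 5.17 | 31% | 35% |
| 2, 4, 6, 8, 10 | 6.00 | 39% | 45% |
| 5 at session 1, then linear to 10 | 7.36 | 54% | 62% |
| 5, 8, 10, 10, 10 | 8.60 | 68% | 75% |
| 7.5 at session 1, then linear to 10 | 8.68 | 68% | 76% |

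At 37 per group, 80% power needs a mean difference of 10.0 mm; at 44 it needs 9.2 mm. A profile that is lower early and ends at exactly 10 mm has a mean below 10 mm, so at 37 per group its power is below 80%. The size of the loss depends on the profile.

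**The case against.** The strongest case for the plan is that it sized what it analyses first. The Statistics section does name an integral effect over the same five readings, and a repeated-measures formula with r = 5 is a coherent way to size a comparison over the whole course. This stands. The averaged target is legitimate, and the arithmetic behind 37 is correct. The match is only at best, because the planned ANOVA takes baseline as one of six time levels while the formula adjusts for it; that is a separate matter, not pursued here.

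Two stronger readings are tempting, and the documents do not support them.

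- A reader might infer that the formula assumes 10 mm at every reading. It needs only a 10 mm average. A build-up of 3.3, 6, 10, 14 and 16.7 mm sums to 50, averages 10, and keeps 80% power at 37 per group and 86% at 44. An accumulating benefit is thus compatible with the sizing.
- A reader might infer that the trial hypothesises a benefit that starts small and reaches 10 mm only at session 12, so that even the averaged comparison has far less than 80% power. The protocol states no time course and no 10 mm target for session 12, and it seeks an effect directly after session 1 as well. How far power falls depends on the assumed profile: with an early rise, the shortfall at 44 per group is modest.

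It can also be said that a time-specific contrast is detail for a statistical analysis plan, which is not shown. The mismatch does not depend on that: the protocol itself fixes δ, r, P and n in one section and the single-reading definitions and tests in another.

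**Conclusion.** The point holds in this form: the 80% applies to a 10 mm difference in the baseline-adjusted mean of five readings and to nothing else that the protocol names. For 10 mm at session 1 or at session 12, power at 37 to 44 per group is about 53% to 61% with baseline adjustment and about 31% to 36% with the planned unadjusted t test; with 35 completers it is 51% and 29%. These figures need no assumed time course. They rest on the protocol's σ and ρ, the same at every reading, and on normal-approximation power.

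The further loss for the five-reading mean is conditional. If the benefit rises to only 10 mm at session 12, power lies at about 26% to 68% at 37 per group, and up to about 76% at 44, over the profiles tried. This is a misdescribed power claim, not an arithmetic error in the 37.

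**What to change.** 1. In the Sample size section, state that δ is the difference in the baseline-adjusted mean of the five post-treatment readings, session 1 included, and that the 80% refers to this average.
2. In the same place, give the power for 10 mm at session 1 and at session 12: with baseline adjustment, 53% at 37 per group, about 61% at 44 and 51% at 35 completers.
3. In the Statistics section, replace the unadjusted t tests for the immediate and accumulated effects by baseline-adjusted differences at session 1 and session 12, each with a 95% confidence interval. At 44 per group, this reduces the standard error from 6.29 mm (29.5 × √(2/44)) to 4.49 mm. A null result at session 12 can then be judged by whether the interval still includes 10 mm.
4. Keep the five-reading average as the integral effect. Dropping it in favour of session 12 would exchange one legitimate target for another, and the documents give no reason to do so.

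The cost is some rewording, two contrasts and a less favourable stated power. No extra patients are needed. The Trial status section reports that recruitment of 88 is complete and that treatment and follow-up continue, so the change should be fixed before the data are analysed.

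### Eighty-eight patients cover a loss of about 16%, not the 20% the protocol allows for: 44 per group less 20% leaves 35, below the 37 required

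*Protocol article*

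**What the plan says.** Everything needed is in the Sample size section of the protocol article. It sets out a repeated-measures formula with one pre-treatment and five post-treatment VAS measurements, the last of them at the end of the 12th treatment, and 1:1 allocation. From this, "an estimated sample size of 37 patients per group was obtained". The loss allowance follows: "Considering a possible loss to follow-up of 20% Additional file 2, we planned to include total of 88 patients in our study". The section does not show how the 20% was applied.

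Power is not written as a percentage. It is fixed by "μ_β_ = 0.8417", the normal quantile for 80%. The Trial status section reports that recruitment of all 88 participants is complete.

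**The concern.** A loss allowance has one purpose: the number left after the assumed loss should still meet the calculated requirement. Here the requirement, the loss rate and the total are printed together and do not agree. A reader would take it that 88 patients keep the power at 80% if a fifth of them are lost. If that is not so, the evaluable number and the power are both lower than the section implies, and the results paper may repeat the statement.

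**Working it through.** **Inputs, all from the Sample size section**

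- Significance level: "α = 0.05 (bilateral); μ_α_ = 1.96"
- Power: "μ_β_ = 0.8417", i.e. 80%
- Difference δ: 10 mm ("assuming that a minimal difference of δ = 10 mm is considered as a clinically significant relief of chronic pain")
- Standard deviation σ: 29.5 mm ("with a standard deviation (σ) of 29.5 mm of the VAS score for knee pain in all patients prior to treatment")
- Correlation ρ: 0.70
- Measurements before treatment, P = 1 ("VAS score before the first intervention, one time point before treatment"); after treatment, r = 5
- Loss: 20%; planned total: 88, so 44 per group

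**Step 1: reproduce the protocol's 37**

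Variance factor = [1/r + (1 − 1/r)ρ] − ρ²/[1/P + (1 − 1/P)ρ] = [0.2 + 0.8 × 0.70] − 0.49/1 = 0.76 − 0.49 = 0.27

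n = 2 × 29.5² × (1.96 + 0.8417)² / 10² × 0.27 = 36.89, so 37 per group. This agrees with the protocol.

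**Step 2: apply the loss**

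- Evaluable from the planned number: 44 × (1 − 0.20) = 35.2 per group, against 37 required.
- Number needed: 37 / (1 − 0.20) = 46.25, so 47 per group and 94 in total. The difference from 88 is 6 patients.
- Loss that 44 per group can absorb: 1 − 37/44 = 0.159, or 15.9%.

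**Step 3: where 88 probably comes from**

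37 × 1.2 = 44.4, which rounds down to 44 per group and 88 in total. This is a reconstruction, since the section gives no working. Even with that rule, rounding up would give 45 per group (90 in total), and 45 × 0.8 = 36 is still short of 37.

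**Step 4: power**

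Power ≈ Φ(δ / [σ√(2 × 0.27/n)] − 1.96). At n = 35: 10 / (29.5 × √(0.54/35)) − 1.96 = 2.729 − 1.96 = 0.769, and Φ(0.769) = 0.779.

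| Analysed per group | Normal approximation | t distribution |
|---|---|---|
| 35 (44 less 20%) | 77.9% | 76.7% |
| 37 (required) | 80.1% | 79.1% |
| 44 (no loss) | 86.4% | 85.7% |

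Compared like with like, the drop is a little over 2 percentage points by either method.

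**The case against.** The arithmetic is hard to dispute; the arguments on the other side concern its weight.

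*The shortfall is conditional.* The 20% is described as a possible loss, and the five post-treatment measurements in the formula stop at the 12th treatment, as does the repeated measures ANOVA in the Statistics section. Patients lost only during the one-month follow-up would cost that analysis nothing, and with all 44 per group analysed power is about 86%. This stands as a condition on the size of the effect. It does not rescue the statement, because the protocol itself offers the 20% as the reason for going from 37 per group to 88 in total. A repeated measures ANOVA in its standard form also uses only patients with every measurement, so loss at any point up to the 12th treatment counts.

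*Two points of power lie well within the uncertainty of the inputs.* The protocol gives "ρ = 0.70 (usually between 0.50 and 0.75" as the usual range. Across it the formula requires 47.8 per group at ρ = 0.50 (factor 0.35) and 32.4 at ρ = 0.75 (factor 0.2375), and power at 35 per group runs from about 67% to about 83%. This is fair, and it is why the point is minor. But uncertainty in ρ does not make 44 × 0.8 reach 37.

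*Little can be done now.* Recruitment is complete, and the final confidence interval will reflect the number actually analysed. That is true as well, and it limits the remedy to correcting the wording.

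**Conclusion.** The point holds. On the protocol's own figures, 88 patients do not cover a 20% loss. They cover 15.9%, and at 20% about 35 per group remain against the 37 required. The effect is small: about two evaluable patients per group, and power of 77.9% instead of 80.1%. It is a definite arithmetic error in a figure that readers rely on, but it does not threaten the trial.

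The power figures rest on the protocol's δ, σ and ρ, on the full 20% being missing from the analysed time points, and on an analysis that adjusts for baseline as the formula assumes. The 15.9% and the shortfall from 94 depend only on the 37, the 88 and the 20%.

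**What to change.** Replace the sentence on loss with one the numbers support, for example: 88 patients (44 per group) retain the required 37 evaluable per group with up to about 16% loss by the 12th treatment; with 20% loss, about 35 per group remain and power is about 78%. Stating the intended 80% power as a percentage alongside would help, since it can now be read only from the quantile.

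The cost is one sentence and a slightly less favourable stated figure. Enrolment, trial conduct and the analysis are unchanged. The results paper should carry the corrected statement.
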